## 9.2.4 Assessment of safety outcomes

### 9.2.4.1 Serious adverse events

Recording of information about adverse reactions during the study includes:

- Time of onset
- Duration
- Resolution
- Action to be taken
- Assessment of intensity
- Relationship with study treatment

For definition and procedures please refer to section 10. All SAE detected by the medical personnel of the Division of Infectious Diseases and Hospital Epidemiology, Kantonsspital St. Gallen will be attended immediately and reported on a timely basis to the EC. During study visits participants will be examined and questioned by the medical personnel about their health status. In case of any SAE a questionnaire will be made by the medical personnel including all points described above. Spontaneous reports will also be made in case a SAE occurs and the participants attend for medical attention outside the study visits time frame.

#### **9.2.4.2 Vital signs**

Body temperature, heart beat and blood pressure will be monitored in every study visit.

#### **9.2.5 Assessments in participants who prematurely stop the study**

If a subject withdraws during the interventional phase of the study and does not consent to continued follow-up of associated clinical outcome information, the investigator will not access, for purposes related to the study, the subject's medical record or other confidential records requiring the subject's consent.

If a subject withdraws during the interventional phase of the study but agrees to continue with the follow up of associated clinical outcome information, the following measures for data collection will be taken depending on the time point of withdrawal: a) Data from anti-porins specific immune responses will only be included in the analysis when the patient withdraws after visit 5, and b) Data from patients withdrawn at early time points will only be used for the genetic analysis of live attenuated bacteria contained in the formulation (applicable for study subjects that withdrawn after visit 3).

### **9.3 Procedures at each visit**

The screening visit should be performed within 7 days prior to visit number 2, when the first vaccine dose will be administrated. It is responsibility of the investigator to obtain written informed consent from each patient participating in this study after adequate face to face explanation of the aims, methods, objectives and potential hazards of the study. The patients who agree to participate in the study must sign the informed consent form during the screening visit prior to any study-related assessment or procedure.

#### **9.3.1 Visit 1. Screening visit, day -7.**

Recruitment of study subjects

Obtaining Informed Consent

Obtaining medical history and information used to apply inclusion and exclusion criteria

Physical examination and measurement of vital signs to evaluate the overall health status of the study subjects

Urine pregnancy test

HIV test

#### **9.3.2 Visit 2. Intervention visit, day 0.**

Enrolment in the study of participants that fulfil eligibility criteria (refer to section 7.1)

Measurement of vital signs

Blood sample collection to be used as a control before vaccination for the evaluation of specific anti-porins immune responses.

Stool sample collection to be used as control for the evaluation of anti-porins immune responses (determination of specific IgA antibodies against *S. Typhi* porins) before the vaccine administration and as a control for the evaluation of genetic changes of live attenuated bacteria contained in the formulation.

Administration of first vaccine dose.

Reporting of SAE starts at this time point and lasts until the end of the study.

### **9.3.3 Visit 3. Intervention visit, day 2.**

Measurement of vital signs

Second vaccine dose administration

Stool sample collection for evaluation of genetic changes of live attenuated bacteria contained in the formulation

### **9.3.4 Visit 4. Intervention visit, day 4.**

Measurement of vital signs

Third vaccine dose administration

Stool sample collection for evaluation of genetic changes of live attenuated bacteria contained in the formulation

### **9.3.5 Visit 5. Intervention visit, day 6.**

Measurement of vital signs

Blood sample collection for evaluation of specific anti-porins immune responses (day 7 after last immunization)

Stool sample collection for evaluation of genetic changes of live attenuated bacteria contained in the formulation and for determination of IgA antibodies (day 7 after last immunization)

### **9.3.6 Visit 6. Follow-up visit, day 27.**

Measurement of vital signs

Blood sample collection for evaluation of specific anti-porins immune responses (day 21 after last immunization)

Stool sample collection for determination of IgA antibodies (day 21 after last immunization)

### **9.3.7 Visit 7. Follow-up visit, day 60.**

Measurement of vital signs

Blood sample collection for evaluation of specific anti-porins immune responses (day 56 after last immunization)

Stool sample collection for determination of IgA antibodies (day 56 after last immunization)

## 10. SAFETY

### 10.1 Drug studies

The new law on clinical research (ordinance ClinO) does not require the documentation of adverse events (AEs) for Category A drug trials, therefore during the entire duration of the study only SAE will be collected, fully investigated and documented in source documents and case report forms (CRF). Study duration encompassed the time from when the participant signs the informed consent until the last protocol-specific procedure has been completed, including a safety follow-up period.

#### 10.1.1 Definition and assessment of (serious) adverse events and other safety related events

An **Adverse Event** is any untoward medical occurrence in a patient or a clinical investigation participant administered a pharmaceutical product and which does not necessarily have a causal relationship with the study procedure. An AE can therefore be any unfavourable and unintended sign (including an abnormal laboratory finding), symptom, or disease temporally associated with the use of a medicinal (investigational) product, whether or not related to the medicinal (investigational) product. [ICH E6 1.2]

A **Serious Adverse Event** is classified as any untoward medical occurrence that:

- results in death,
- is life-threatening,
- requires in-patient hospitalization or prolongation of existing hospitalisation,
- results in persistent or significant disability/incapacity, or
- is a congenital anomaly/birth defect.

In addition, important medical events that may not be immediately life-threatening or result in death, or require hospitalisation, but may jeopardise the patient or may require intervention to prevent one of the other outcomes listed above should also usually be considered serious. [ICH E2A]

SAEs should be followed until resolution or stabilisation. Participants with ongoing SAEs at study termination (including safety visit) will be further followed up until recovery or until stabilisation of the disease after termination.

#### *Assessment of Causality*

Both Investigator and Sponsor-investigator make a causality assessment of the event to the study drug, based on the criteria listed in the ICH E2A guidelines:

| Relationship | Description                                                                                                               |
|--------------|---------------------------------------------------------------------------------------------------------------------------|
| Definitely   | Temporal relationship
Improvement after dechallenge*
Recurrence after rechallenge
(or other proof of drug cause) |
| Probably     | Temporal relationship
Improvement after dechallenge
No other cause evident                                          |
| Possibly     | Temporal relationship
Other cause possible                                                                             |
| Unlikely     | Any assessable reaction that does not fulfil the above conditions                                                         |

|                                                                                         |                                      |
|-----------------------------------------------------------------------------------------|--------------------------------------|
| Not related                                                                             | Causal relationship can be ruled out |
| *Improvement after dechallenge only taken into consideration, if applicable to reaction |                                      |

#### *Unexpected Adverse Drug Reaction*

An “unexpected” adverse drug reaction is an adverse reaction, the nature or severity of which is not consistent with the applicable product information (e.g. Investigator’s Brochure for drugs that are not yet approved and Product Information for approved drugs, respectively). [ICH E2A]

#### *Suspected Unexpected Serious Adverse Reactions (SUSARs)*

The Sponsor-Investigator evaluates any SAE that has been reported regarding seriousness, causality and expectedness. If the event is related to the investigational product and is both serious and unexpected, it is classified as a SUSAR.

#### *Assessment of Severity*

The severity grading scale used for this study will be in accordance to the grades for severity described in the “Common Terminology Criteria for Adverse Events v4.03 (CTCAE), June 14, 2010”. Grade scales are summarized as follows:

Grade refers to the severity of the AE. The CTCAE displays Grades 1 through 5 with unique clinical descriptions of severity for each AE based on this general guideline:

*Grade 1 Mild*; asymptomatic or mild symptoms; clinical or diagnostic observations only; intervention not indicated.

*Grade 2 Moderate*; minimal, local or noninvasive intervention indicated; limiting age-appropriate instrumental ADL (instrumental Activities of Daily Living: refer to preparing meals, shopping for groceries or clothes, using the telephone, managing money, etc).

*Grade 3 Severe or medically significant but not immediately life-threatening*; hospitalization or prolongation of hospitalization indicated; disabling; limiting self-care ADL (self-care ADL: refer to bathing, dressing and undressing, feeding self, using the toilet, taking medications, and not bedridden).

*Grade 4 Life-threatening consequences*; urgent intervention indicated.

*Grade 5 Death related to AE.*

### **10.1.2 Reporting of serious adverse events and other safety related events**

#### **Reporting of SAEs**

All SAEs must be reported immediately and within a maximum of 24 hours to the Sponsor-Investigator of the study. The Sponsor-Investigator will re-evaluate the SAE and return the form to the site.

SAEs resulting in death are reported to the local Ethics Committee (via local Investigator) within 7 days.

#### **Reporting of SUSARs**

A SUSAR needs to be reported to the local Ethics Committee (local event via local Investigator) within 7 days, if the event is fatal, or within 15 days (all other events).

#### **Reporting of Safety Signals**

All suspected new risks and relevant new aspects of known adverse reactions that require safety-related measures, i.e. so called safety signals, must be reported to the Sponsor-Investigator within 24 hours. The Sponsor-Investigator must report the safety signals within 7 days to the local Ethics Committee (local event via local Investigator).

## Reporting and Handling of Pregnancies

Pregnant participants must immediately be withdrawn from the clinical study. Any pregnancy during the treatment phase of the study and within 30 days after discontinuation of study medication will be reported to the Sponsor-Investigator within 24 hours. The course and outcome of the pregnancy should be followed up carefully, and any abnormal outcome regarding the mother or the child should be documented and reported.

For all procedure regarding reporting of serious adverse events and other safety related events there will be Standard Operating Procedures (SOPs) in place.

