### **7.4 Criteria for withdrawal / discontinuation of participants**

Study participants are withdrawn from the study in the following cases: a) withdrawal of informed consent, b) non-compliance and c) presence of SAE due to an unknown health condition of the participants or any other cause that compromise the integrity of participants.

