### **8.2 Administration of experimental and control interventions**

#### **8.2.1 Experimental Intervention**

3 doses of the vaccine are to be administered in alternate days (0, 2 and 4). Vaccine potency is dependent upon storage under refrigeration [between 2 °C and 8 °C (35.6 °F– 46.4 °F)]. The vaccine should be stored under refrigeration at all times. One capsule is to be swallowed approximately 1 hour before a meal with a cold or lukewarm [temperature not to exceed body temperature, e.g., 37 °C (98.6 °F)] drink. Care should be taken not to chew the vaccine capsule. The vaccine capsule should be swallowed as soon after placing in the mouth as possible.

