### **8.3 Dose / Device modifications**

Post-marketing surveillance has revealed that adverse reactions are infrequent and mild. Adverse reactions reported to the manufacturer during 1991–1995, time in which over 60 million doses (capsules) were administered included: diarrhea (N = 45), abdominal pain (N = 42), nausea (N = 35), fever (N = 34), headache (N = 26), skin rash (N = 26), vomiting (N = 18), or urticaria in the trunk and/or extremities (N = 13). One isolated, non-fatal anaphylactic shock considered to be an allergic reaction to the vaccine was reported. This adverse reactions show that the vaccine is relatively safe and therefore the expected adverse reactions will be infrequent and mild as described above.

Nevertheless in case of any SAE or in direct request from a participant to withdraw from the study, the vaccine administration will be stopped and the appropriate medication/treatment will be applied until the complete recovery of the study subjects.

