## **8.5 Data Collection and Follow-up for withdrawn participants**

If a subject withdraws during the interventional phase of the study and does not consent to continued follow-up of associated clinical outcome information, the investigator will not access, for purposes related to the study, the subject's medical record or other confidential records requiring the subject's consent.

If a subject withdraws during the interventional phase of the study but agrees to continue with the follow up of associated clinical outcome information, the following measures for data collection will be taken depending on the time point of withdrawal: a) Data from anti-porins specific immune responses will only be included in the analysis when the participant withdraws after visit 5, and b) Data from study subjects withdrawn at early time points will only be used for the genetic analysis of live attenuated bacteria contained in the formulation (applicable for study subjects that withdraw after visit 3).

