### **11.5 Handling of missing data and drop-outs**

An available data analysis will be performed, thus, missing data will not be imputed. A common problem in clinical trials is the missing data that occurs when patients do not complete the study and drop out without further measurements. Missing data cause the usual statistical analysis of complete or all available data to be subject to bias. There are no universally applicable methods for handling missing data. In this study the following measures will be taken:

- (1) Reasons for dropouts and proportions for each treatment group will be reported. Characteristics for participants who did or did not drop-out of the study will be compared to determine if there are any clinically relevant differences between the two groups.
- (2) Careful conduction of the study will be made to minimize the chance of dropouts.
- (3) Post-dropout data will be collected on the primary endpoints, if at all possible.
- (4) Depending on the time frame of the study drop-outs could be replaced, with previous authorization from the investigator and the sponsor.

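### Pregnancy and certain SAEs end study participation, not just dosing, and 8.5(a)/9.2.5 bar early leavers' immune data that 11.4.1 includes

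*Protocol*

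**What the plan says.** **Exit rules.** Under Section 10.1.2, "Pregnant participants must immediately be withdrawn from the clinical study". No arm or study day is exempt. Section 7.4(c) withdraws participants from the study on "presence of SAE due to an unknown health condition of the participants or any other cause that compromise the integrity of participants". Section 8.3 acts on dosing: "in case of any SAE or in direct request from a participant to withdraw from the study, the vaccine administration will be stopped". It does not say whether the participant then stays for later visits.

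**Timing.** Vaccine is given on days 0, 2 and 4 (8.2.1), and the five controls get none (Synopsis). The primary endpoints are measured at Visits 2, 5, 6 and 7 (9.2.1). All post-baseline primary samples therefore come after the last dose. SAEs are sought at each visit: "During study visits participants will be examined and questioned by the medical personnel about their health status" (9.2.4.1).

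**After an exit.** Section 11.5(3) states "Post-dropout data will be collected on the primary endpoints, if at all possible". Section 11.5(4) adds "Depending on the time frame of the study drop-outs could be replaced, with previous authorization from the investigator and the sponsor". Sections 10.1.1 to 10.1.3 follow known SAEs and pregnancies. For a participant who withdraws in the interventional phase but agrees to further follow-up, Section 8.5(a) says "Data from anti-porins specific immune responses will only be included in the analysis when the participant withdraws after visit 5", and 9.2.5 repeats this.

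**Analysis set.** Section 11.4.1 takes in every vaccinee who had all three doses and every randomised control. It makes no exception for withdrawal.

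**The concern.** Stopping a vaccine and leaving a study are different acts. Here the first is complete by day 4, yet two rules impose the second up to day 60, and in controls from the start. An exit in that period protects nobody from vaccine. It interrupts the samples that carry the primary endpoints and the scheduled questioning about new SAEs.

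The protocol then works against its own remedy. Section 11.5(3) asks for primary-endpoint data after dropout, but 8.5(a) and 9.2.5 keep those data out of the immune analysis when the exit came before Visit 5. Section 11.4.1 would include the same person. Two analysts following different sections would analyse different sets of participants.

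An exit between Visits 5 and 7 has a milder effect. The participant's Visit 5-7 mean, used in the between-group Mann-Whitney test (11.4.3), may rest on one or two visits. Replacement restores the number of participants, not the later data of the one who left.

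**Working it through.** The protocol gives no sample-size calculation, dropout rate or SAE rate, so there is no figure of its own to reproduce. The check has two parts: the size of the possible loss, and the conflict between sections.

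**Inputs from the protocol.** Last dose on day 4; Visits 5, 6 and 7 on days 11, 25 and 60 (schedule table and 9.1); 15 vaccinees and 5 controls. The headings of 9.3.5 and 9.3.6 give days 6 and 27. I use the table days because they match the stated 7, 21 and 56 days after the last dose: 4 + 7 = 11, 4 + 21 = 25, 4 + 56 = 60.

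**Assumptions, not in the protocol.** Exits spread evenly over days 4 to 60; a fraction r of later samples recovered under 11.5(3); 10 to 20 women, split 3:1 over the arms, with 1-10% pregnancies per year; SAEs in 0.5-2% of participants over 60 days.

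**1. Period with nothing left to stop (vaccinees).** 60 - 4 = 56 days, and 56/60 = 93% of the time after first dose. For controls it is the whole period.

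**2. Immune-sampling visits missing per exit after day 4.** The windows are days 4-11 (7 days, 3 visits at risk), 11-25 (14 days, 2 visits) and 25-60 (35 days, 1 visit). With 8.5(a) excluding exits before Visit 5 whatever is recovered:

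mean missing = [7×3 + (14×2 + 35×1)(1 - r)]/56 = [21 + 63(1 - r)]/56

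- r = 0: 84/56 = 1.5 of 3
- r = 0.5: 52.5/56 = 0.94
- r = 1: 21/56 = 0.375

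If 8.5(a) followed 11.4.1, the formula would be 84(1 - r)/56, giving 1.5, 0.75 and 0. The 0.375 at full recovery is due to 8.5(a) alone.

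**3. Expected pregnancies where exit stops no exposure.** Pregnancies per year: 10×0.01 = 0.1 to 20×0.10 = 2.

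- Vaccinees, days 4-60: 0.75×0.1×56/365 = 0.012 to 0.75×2×56/365 = 0.230
- Controls, days 0-60: 0.25×0.1×60/365 = 0.004 to 0.25×2×60/365 = 0.082
- Sum: 0.016 to 0.31
- Before Visit 5, high end: 0.75×2×7/365 + 0.25×2×11/365 = 0.029 + 0.015 = 0.044; low end 0.044/20 = 0.002

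For the assumed rates these counts are upper limits, because no pregnancy test is scheduled after Visit 1 and an unrecognised pregnancy triggers no exit.

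**4. Expected SAEs of any kind.** 20×0.005 = 0.1 to 20×0.02 = 0.4. Only some would fall under 7.4(c).

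**5. The sections side by side.**

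| Participant who agrees to follow-up | 8.5(a)/9.2.5 | 11.4.1 |
|---|---|---|
| Vaccinee, exit before third dose | out | out |
| Three-dose vaccinee, exit before Visit 5 (days 4-11) | out | in |
| Control, exit before Visit 5 (days 0-11) | out | in |
| Three-dose vaccinee or control, exit after Visit 5 | in | in |

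The second and third rows conflict, whatever the reason for leaving.

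**6. Weight of one participant.** One exit is 1/5 = 20% of controls or 1/15 = 7% of vaccinees. If one participant's data were lost altogether, a rough normal approximation, Φ(d/√(1/n₁ + 1/n₂) - 1.96) with an assumed shift d = 1.5 SD, gives power 0.83 for 15 v 5, 0.76 for 15 v 4 and 0.82 for 14 v 5.

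**The case against.** **Much of the remedy already exists.** Section 11.5(3) seeks post-dropout primary data, 10.1.1 to 10.1.3 follow known SAEs and pregnancies, and 9.2.4.1 provides for spontaneous SAE reports outside visits. This stands. A reader might infer that an exit loses the data or ends safety follow-up; the protocol does not support that. What remains open is scheduled questioning about new SAEs and samples that are sought only where possible.

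**Section 7.4(c) is not automatic.** A reader might infer that it leaves the investigator no discretion. Deciding whether an SAE compromises the participant is a clinical judgement, so that reading is too strong. The rule is unconditional only once it is judged to apply.

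**Withdrawing a pregnant volunteer can be a protective choice.** Stopping exposure is not the only reason to end research sampling. This stands too, and is why sampling should depend on consent and on a judgement that it is safe.

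**Section 8.5 covers only withdrawal in the interventional phase.** If that phase meant only the dosing days, 8.5(a) would not reach exits after day 4 and the 0.375 would vanish. The text does not bear this out. Item (a) itself provides for withdrawal after Visit 5, and 9.3.5 labels Visit 5 an intervention visit. The phase therefore runs past day 4.

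**The effect is tiny and partly generic.** At the assumed pregnancy rates with no recovery, about 0.02 to 0.48 visits would be missing out of 20×3 = 60: the high end is 0.230×1.5 + (0.5/365)×(11×3 + 14×2 + 35×1) = 0.345 + 0.132, and the low end is one twentieth of that. The control-arm signed-rank test cannot reach 0.05 even with all five (2/2⁵ = 0.0625). Any missed visit shortens the Visit 5-7 mean under an available-data analysis. All of this stands and sets the priority.

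**Conclusion.** The point holds at low priority, in two parts.

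- **Firmer part:** 8.5(a) and 9.2.5 contradict 11.4.1 for three-dose recipients who leave between day 4 and Visit 5 and for controls who leave before Visit 5. They exclude immune data that 11.5(3) asks the site to collect. This follows from the text and needs no assumed rate.
- **Softer part:** 10.1.2 and 7.4(c) end participation when only dosing needs to stop, and no section says that the participant may stay for the remaining visits. The data are at risk, not necessarily lost.

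Per exit after day 4 the average loss is between 0.375 and 1.5 of 3 immune-sampling visits, depending on recovery and assuming even timing of exits. Expected counts are small: 0.016 to 0.31 pregnancies where exit stops no exposure, 0.002 to 0.04 of them before Visit 5, and 0.1 to 0.4 SAEs of which only some count. These rest on assumed rates. A reader might infer that the rules endanger the trial's main result; with few or no events expected in an uncalculated pilot, the documents do not support that.

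**What to change.** 1. Amend 8.5(a) and 9.2.5 so that all available immune data from three-dose recipients and from all controls are analysed, as 11.4.1 states.
2. In 10.1.2 and 7.4(c), state that the event stops any further doses and that the participant is invited to the remaining visits for SAE questioning, with sampling only if she or he consents and the investigator judges it safe.
3. Note that the pregnancy exclusion in 7.1 applies at entry and does not bar this follow-up.

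The cost is wording in four sections and matching consent text, with no added visits, tests or staff. If made after approval, the change may count as a substantial amendment needing ethics committee approval (2.10).
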